### Statistical methods

Data from the trial will be analyzed using STATA software version 14.0 (Stata Corp, College Station, Texas, USA). All data will be checked for accuracy and a missing data analysis will be undertaken. The trial will adhere to the ‘CONSORT statement: extension to cluster randomized trials’ [34]. The data will be analyzed on an intention-to-treat basis, based on patient assignment.

A mixed linear regression model will be adopted to compare the significant differences between groups over a 12-month period. The mixed linear regression model will be adjusted by baseline value and potential confounding variables, for example, the sites and staff education levels [35]. Two-sided tests will be performed for all analyses and the level of significance will be set at *P* < 0.05. Where appropriate, 95% confidence interval will also be reported along with the *P* values.

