**Methods:**

A cluster randomized controlled trial will be applied to the study. Fourteen nursing homes will be randomly allocated to either the intervention group (*n* = 7) or the control group (*n* = 7). Forty staff will be recruited from each nursing home and the estimated sample size will be 280 staff in each group. The intervention includes a structured, evidence-based quality improvement education program for staff to facilitate knowledge translation in evidence-based quality improvement targeting urinary incontinence, pressure injury and falls prevention. The primary outcomes are nursing homes’ capacity to create and sustain quality improvement, staff perceptions of person-centered care, self-reported quality of care by residents and selected quality indicators at 12 months follow-up adjusted for baseline value. Secondary outcomes are residents’ quality of life, residents’ unplanned admissions to acute care hospitals, quality of care reported by staff, staff job satisfaction and staff intention to leave adjusted for baseline value. A mixed linear regression model will be adopted to compare the significant differences between groups over a 12-month period.

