### Participants and sample size

Participants will be staff who provide direct care for residents. The sample size is based on one of the primary outcomes: staff perceptions of person-centered care measured by the ‘Approaches to Dementia Questionnaire’ (ADQ). In an earlier cluster RCT to improve care quality and safety through a 12-month clinical leadership program in aged care [24], the researchers found no differences in care staff attitudes toward dementia and dementia care assessed by ADQ between the intervention and control sites at 12 months post-intervention. Therefore, in our study, we have set a clinically meaningful change of 1.0 ADQ scores and 85% power to detect a difference of 1.2 standard deviation between groups at the 5% level of significance.

Since randomization will be conducted by the nursing homes (clusters), the sample size was adjusted to take into account the design effect. We have considered a large intra-class correlation coefficient of 0.26 (average estimate from a nursing home staff training intervention carried out in England and Wales [25]) and an average cluster size of 40 nursing staff. Assuming an alpha error of 0.05 and a beta error of 20%, the required cluster number was 7 for each group (251 nursing staff per group). Allowing for an attrition rate of 10–12%, we would require around 280 staff in each arm of the project.

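### With 14 randomised homes, the mixed-model analysis secures no small-sample reference; if the arm effect is tested against a normal distribution, the 5% level becomes about 7.4% (REML) or 9.5% (ML)

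*Protocol article*

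**What the plan says.** The protocol article's abstract (Methods) gives the number of clusters: "Fourteen nursing homes will be randomly allocated to either the intervention group" or the control group, seven homes to each. Participants and sample size agrees: "the required cluster number was 7 for each group", with 251 staff per group, an intra-class correlation (ICC) of 0.26 and an average of 40 staff per home.

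Statistical methods sets out the inference:

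- Model: "A mixed linear regression model will be adopted to compare the significant differences between groups over a 12-month period".
- Covariates: the model is "adjusted by baseline value and potential confounding variables, for example, the sites and staff education levels".
- Software: "Data from the trial will be analyzed using STATA software version 14.0".
- Level: "Two-sided tests will be performed for all analyses and the level of significance will be set at" P < 0.05.
- Intervals: "Where appropriate, 95% confidence interval will also be reported along with the" P values.

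The article does not state the random-effect structure, the choice between ML and REML, or whether the arm effect is referred to a normal distribution, a t distribution or a permutation distribution. Homes are grouped by ownership and size for allocation (Randomization), but these two factors are not among the covariates given as examples.

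**The concern.** The arm effect is a contrast between homes. With 7 homes per arm, the variance that governs it is estimated from 14 − 2 = 12 degrees of freedom. About 250 staff per arm do little to help when most of the variance lies between homes. A normal reference treats that variance as known. ML also underestimates it, because it divides by the number of homes rather than by the residual degrees of freedom. Either way, the test rejects too often and the intervals are too short.

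Borderline results are at stake. Under REML, an estimate/SE ratio between 1.96 and 2.18 would be called significant with a normal reference but not on 12 degrees of freedom. Under ML, on its own smaller standard error, the disputed band is 1.96 to 2.35 (2.179 × √(14/12)). If the reference is still open when results are seen, that choice could decide a primary outcome.

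**Working it through.** **Inputs.** 14 homes, 7 per arm (abstract; Participants and sample size). ICC 0.26, 40 staff per home, alpha 0.05, beta 20%, attrition 10–12% (Participants and sample size). Two-sided 5% level and 95% intervals (Statistical methods). Assumptions not in the article: a random intercept for home, equal home sizes, a continuous outcome, and 36 analysed staff per home (40 less 10%).

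**1. The plan's own figure.** Take a difference of 1.0 and read 1.2 as the standard deviation:

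- Unadjusted n per group = 2 × 1.2² × (1.960 + 0.8416)² / 1.0² = 22.60.
- Design effect = 1 + 39 × 0.26 = 11.14.
- 22.60 × 11.14 = 251.8 per group, and 251.8 / 40 = 6.3 homes, rounded up to 7.

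This matches the stated 251 and 7. It uses normal quantiles with no allowance for the number of homes. At 85% power, which the same section also mentions, the result would be 288. With 7 homes of 40 per arm, power is 84.0% on a normal reference and 77.4% on t with 12 df. The stated 80% is therefore met only with the normal reference.

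**2. Where the variance lies.** The between-home share of the variance of the arm difference is 0.26 / (0.26 + 0.74/36) = 0.927. About 93% of the uncertainty rests on 14 home means.

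**3. Error with a normal reference.** In a balanced design with df = 14 − 2 − (number of home-level covariates):

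- REML: error = P(|t_df| > 1.96)
- ML: error = P(|t_df| > 1.96 × √(df/14))

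| Home-level covariates | df | REML error (coverage) | ML error (coverage) |
|---|---|---|---|
| 0 | 12 | 7.4% (92.6%) | 9.5% (90.5%) |
| 1 | 11 | 7.6% (92.4%) | 11.0% (89.0%) |
| 2 | 10 | 7.8% (92.2%) | 12.9% (87.1%) |

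**4. Simulation under the null, no home-level covariate, 36 or 40 staff per home.**

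| ICC | REML, normal | ML, normal | REML, t on 12 df |
|---|---|---|---|
| 0.26 | 7.3–7.4% | 9.3–9.5% | 5.0% |
| 0.05 | 7.1–7.3% | 9.1–9.4% | 4.8–4.9% |
| 0.01 | 5.7–5.9% | 6.7–7.0% | 3.6–3.7% |

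The inflation is much the same from ICC 0.05 to 0.26 and fades only when the ICC is very small. There a fixed 12-df reference becomes somewhat conservative. With one to three home-level covariates and matching df, REML with t gives 4.9% at ICC 0.26.

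**5. Cost in interval width.** 2.179 / 1.960 = 1.11 relative to REML with a normal reference. 1.11 × √(14/12) = 1.20 relative to ML with a normal reference.

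**The case against.** The strongest reply is that the article is silent rather than wrong. It names neither a normal reference nor ML, and a condensed article commonly leaves the estimator and degrees-of-freedom method to the full protocol or SAP, which is not shown. Valid inference is compatible with every sentence in Statistical methods. This stands to the extent that nobody can say the trial will have an inflated error rate.

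Several stronger readings are tempting, and the documents do not support them:

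- *The real false-positive rate is 7–13%.* The rate depends on a choice that the article does not report. The upper end also needs ML and two home-level covariates; ownership and size appear only under Randomization.
- *Stata 14.0 settles the method.* Naming a package does not fix its options, and nothing in the article says which were chosen.
- *Every primary and secondary comparison is affected by this amount.* The rates apply to a continuous outcome. They were not computed for the dichotomised quality-of-care item (Table 3) or the adverse-event indicators among the primary outcomes.
- *The range is a bound.* At ICC 0.01 the error is only about 6–7%. If sites entered as fixed effects, the arm effect would not be estimable and these figures would not apply.

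The reply does not dispose of the point. The stated model, level and intervals do not by themselves deliver 5% with 7 homes per arm. The only place where the article reveals a reference distribution is the sample size, and there it is the normal. That does not prove what the analysis will use, but it gives no reason to presume a small-sample correction.

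**Conclusion.** The point holds in conditional form. The stated analysis does not secure its 5% level or 95% coverage with 14 homes. For a continuous outcome with a home random intercept and no home-level covariates, a normal reference gives a true two-sided error of about 7.4% (REML) or 9.5% (ML). Under ML it rises to about 13% if two home-level covariates are added. REML with t on the home-level degrees of freedom restores about 5% at the plan's ICC. This should be fixed before unblinded analysis; it is not evidence that the trial's results will be wrong.

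**What to change.** Add to Statistical methods: *Linear models will be fitted by REML with a random effect for nursing home. Tests and confidence intervals for the arm effect will use Kenward-Roger or Satterthwaite degrees of freedom.* These will be about 12, less any home-level covariates. Make clear that home enters as the random effect and not as a fixed site adjustment.

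For outcomes not analysed by a linear model, base the test on home-level summaries with a t reference, or on a permutation test over the allocations that the stratified randomisation could have produced.

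If the full protocol or SAP already says this, a cross-reference is enough.

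The cost is a sentence, a software option and wider intervals: about 11% wider than REML with a normal reference, or 20% wider than ML with one. Power on the plan's own inputs should then be quoted as about 77%, not 80% or more. No new data are needed.

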### Hypotheses

Primary hypothesis: Nursing homes that implement the ACCM model will report enhanced capacity to create and sustain evidence-based quality (H_1_), improved staff perceptions of person-centered care (H_2_), and higher levels of residents’ or their families’ perception of quality of care (H_3_) compared to the control group.

Secondary hypothesis: Nursing homes that implement the ACCM model will report improved quality of life for residents (H_4_), reduced unplanned admissions to acute care hospitals (H_5_), higher staff perception of quality of care (H_6_), increased job satisfaction for staff (H_7_), and decreased staff intention to leave (H_8_).

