### Outcome measures and data collection

#### Primary outcomes

Primary outcomes include: (i) Nursing homes’ capacity to create and sustain quality improvement; (ii) Staff perceptions of Person-centered Care; (iii) Self-reported quality of care by residents; and (iv) quality indicators that include falls, fall-related injuries, pressure ulcers and urinary incontinence at 12 months follow-up adjusted for baseline value.

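### The outcome list and the hypotheses disagree on what is primary, and four to seven primary tests share one unadjusted 5% threshold with no testing order or success rule

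*Protocol article*

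**What the plan says.** Five places in the protocol article bear on this point.

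- **Primary outcomes.** Four are listed: (i) capacity for quality improvement, (ii) staff perceptions of person-centered care, (iii) residents' own rating of care quality, and (iv) "quality indicators that include falls, fall-related injuries, pressure ulcers and urinary incontinence at 12 months follow-up adjusted for baseline value". No composite or summary score is defined for item (iv). The abstract also counts the indicators as primary.
- **Hypotheses.** The primary hypothesis opens with "Nursing homes that implement the ACCM model will report enhanced capacity to create and sustain evidence-based quality" (H1) and adds H2 (staff perceptions) and H3 (perceived care quality). H4 to H8 are secondary. None covers the indicators. The closest is H5, unplanned admissions, which is a separate secondary outcome.
- **Table 3.** It maps instruments to hypotheses and has no row for the indicators. For H2 it gives the Person-centered Care Assessment Tool.
- **Participants and sample size.** "The sample size is based on one of the primary outcomes", namely staff perceptions of person-centered care, measured there with the Approaches to Dementia Questionnaire (ADQ).
- **Statistical methods.** "Two-sided tests will be performed for all analyses and the level of significance will be set at" P < 0.05. No adjustment, order of testing or success rule follows.

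**The concern.** A reader cannot tell which results would establish the trial's main claim. On the outcome list, a significant fall in pressure ulcers is a primary result; on the hypotheses, it belongs to no stated hypothesis. Nor is it stated whether one, some or all primaries must succeed. Followed as written, the plan lets any single nominally significant result among four to seven be presented as a primary success, so the error rate of the main claim is not the 5% that the threshold suggests. Only one of these outcomes had any bearing on the size of the trial.

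**Working it through.** **Step 1. The plan's own figure.** Inputs from Participants and sample size: difference 1.0; 1.2 read as the standard deviation (an assumption, since the text calls 1.2 the difference in standard deviations); two-sided alpha 0.05; beta 20%; ICC 0.26; cluster size 40.

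- Before clustering: n = 2 × 1.2² × (1.960 + 0.842)² / 1.0² = 22.60 per group.
- Design effect: 1 + (40 − 1) × 0.26 = 11.14.
- Product: 22.60 × 11.14 = 251.8 per group, and 251.8 / 40 = 6.3, rounded up to 7 clusters.

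This reproduces the stated 251 and 7. It uses the full 5% for one outcome. (The 85% power also mentioned in that section gives 288, and reading 1.2 as a standardised difference gives 121. Neither reproduces 251.)

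**Step 2. Number of primary tests.** Outcomes (i) to (iii) give 3. Item (iv) gives 1 if the indicators are combined and 4 if they are tested separately. The range is 3 + 1 = 4 to 3 + 4 = 7.

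**Step 3. Chance of at least one nominally significant primary result when no outcome differs.** For k independent tests:

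- either direction: 1 − 0.95^k
- favouring the intervention only: 1 − 0.975^k

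The rows for correlated tests use normal test statistics with the same correlation between every pair, two-sided.

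| Assumption | 4 tests | 7 tests |
|---|---|---|
| Independent, either direction | 18.5% | 30.2% |
| Correlation 0.3, either direction | 17.4% | 27.1% |
| Correlation 0.5, either direction | 15.6% | 23.0% |
| Correlation 0.7, either direction | 13.0% | 17.8% |
| Independent, favourable only | 9.6% | 16.2% |

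A single test has 5% in either direction and 2.5% in the favourable direction. For two-sided tests on jointly normal statistics, the independent case is the upper limit (Šidák's inequality).

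**Step 4. What a plain Bonferroni split would cost the sized outcome.** Same inputs as Step 1, normal approximation at 251 per group:

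| Level per test | Power | Needed per group for 80%, before attrition |
|---|---|---|
| 0.05 | 80% | 252 |
| 0.05/4 = 0.0125 | 62% | 358 (9 clusters) |
| 0.05/7 = 0.0071 | 54% | 400 (just over 10 clusters) |

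A t test on 12 degrees of freedom, with 7 clusters of 40 per group, gives 77% at 0.05 and 43% at 0.05/7. These losses depend on reading 1.2 as the standard deviation. If 1.2 is the standardised difference, the same t-test calculation gives 97% and 82%. A gated order avoids the loss for the outcome tested first, because that outcome keeps the full 5%.

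**The case against.** **The analysis plan may settle this.** An adjustment or hierarchy is often left to the statistical analysis plan, which is not shown, and a 5% level is compatible with a family-wise procedure at 5%. Silence alone would be no finding. But the article itself declares several primaries and sets one threshold for all analyses, and the clash between Hypotheses and Primary outcomes is on the page. Deciding what is primary belongs in the protocol.

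**All primaries may have to succeed.** H1, H2 and H3 are joined under one primary hypothesis. If all were required, there would be no inflation. The document states no such rule, and that reading still leaves the indicators unplaced.

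**The tempting stronger readings.** A reader might infer that the trial has a 30% chance of a false primary claim. The documents do not support this. That figure needs seven independent tests and counts results in either direction, whereas the hypotheses are directional, and falls and fall-related injuries cannot be independent. Nor does the article say that the four indicators will be tested separately, so seven is the top of a range. A reader might also infer that H2 is properly powered, or must be the lead outcome. The sizing used the ADQ, while H2 is to be measured with another instrument. The stated aim is nearest to H1, and the education modules target the indicators. These objections limit the size and the remedy; they do not remove the contradiction.

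**Conclusion.** The point holds in this form: the document is inconsistent on what is primary, and as written it gives four to seven primary tests one unadjusted threshold without an order or success rule. If any one significant result counts, the error rate of the main claim exceeds that of a single test: at most 18.5% to 30.2% in either direction, and about 16% to 23% at correlation 0.5. In the favourable direction it is about 10% to 16% under independence, against 2.5%. These figures assume that no outcome differs, that each test holds its own level, and a common correlation where one is used. Confidence is high on the contradiction and lower on the exact size, because the correlations and the handling of the indicators are not given.

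**What to change.** 1. Make Hypotheses and Primary outcomes agree: either give the indicators a numbered primary hypothesis or move them out of the primary list. State whether they are combined or tested separately.
2. Before unblinding, state either one primary outcome at two-sided 5% or a procedure that holds the family-wise error at 5%.
3. A natural choice is to test the sized outcome first at 5%. Only if it is significant, test the remaining primaries and the indicators by Holm or in a fixed order. First reconcile the instrument for that outcome (ADQ or Person-centered Care Assessment Tool) and confirm that the sample size applies to it. The sponsor may justify a different lead outcome.

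The cost is wording in the protocol and the registry entry, with no added participants. A gated order takes no power from the lead outcome. The downside is that the other outcomes lose stand-alone primary status and cannot be claimed as confirmed if the lead outcome fails.

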### Economic analysis

The cost-effectiveness of the ACCM model intervention will be evaluated by comparison of the intervention cost to the expected key outcomes. The following model will be used:$$ \mathrm{Cost}\kern0.5em \mathrm{Effectiveness}=\left(\frac{Cost_{New}-{Cost}_{Old}}{Effest_{New}-{Effest}_{Old}}\right) $$

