## Abstract

**Background:**

Residents living in nursing homes usually have complex healthcare needs and require a comprehensive care approach to identifying and meeting their care needs. Suboptimal quality of care is reported in nursing homes and is associated with the poor health and well-being of the residents, the burden on acute care hospitals and the high costs of healthcare for the government.

The aim of this study is to test the hypothesis that an Aged Care Clinical Mentoring Model will create and sustain evidence-based quality improvement in priority areas and will be cost-effective in nursing homes in Hunan Province, China.

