The Clinical Mentors will develop an action plan every three months and discuss the action plan in the regular Steering Committee meetings in order to gain feedback from the Committee to revise or amend the plan. The Clinical Mentor will also receive regular written feedback based on the analysis of outcome measures on baseline data, and at 6 and 12 months post-intervention to foster quality improvement. An Academic Coach, who is an academic member of the University and is specialized in geriatric nursing, will be appointed to support Clinical Mentors to implement the action plan, monitor the process, and update standards, procedures, and in-service education based on the outcomes of the project. The Clinical Mentors and Site Champions will be given paid time of eight hours per week to deliver education modules and mentor staff to translate knowledge at the point of care.

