#### Economic evaluation

Medical costs for each resident will be documented and collected in relation to treatment for fall-related injuries, new pressure ulcers, new urinary tract infections, and visits and readmissions to acute care hospitals. Cost-effectiveness will be expressed through a cost saving ratio and/or the outcomes per cost of intervention.

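### The planned incremental cost-effectiveness ratio changes the meaning of its sign between outcomes and, if medical costs are counted, gives a cost-saving success and a costly failure the same value

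*Protocol article*

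**What the plan says.** The Background of the abstract includes in the study hypothesis that the model "will be cost-effective in nursing homes in Hunan Province, China".

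Two sections say how this will be judged. Economic analysis says "The cost-effectiveness of the ACCM model intervention will be evaluated by comparison of the intervention cost to the expected key outcomes" and introduces, as the model to be applied, the ratio (Cost New - Cost Old)/(Effect New - Effect Old). It does not say which outcomes are the key ones, in which direction they are coded, or which costs are counted. Economic evaluation says "Cost-effectiveness will be expressed through a cost saving ratio and/or the outcomes per cost of intervention". It also lists the costs to be gathered: "Medical costs for each resident will be documented and collected in relation to treatment for fall-related injuries", then new pressure ulcers, new urinary tract infections, and hospital visits and readmissions.

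The primary outcomes include "quality indicators that include falls, fall-related injuries, pressure ulcers and urinary incontinence at 12 months follow-up adjusted for baseline value", for all of which a lower value is better. Unplanned admissions and intention to leave, among the secondary outcomes, should also fall. Capacity for quality improvement, person-centred care, perceived quality of care, quality of life and job satisfaction should rise.

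**The concern.** A ratio of two signed differences discards information. It does not show which of the two differences was negative, and it has a fixed interpretation only if the effect is always coded the same way round. The plan applies such a ratio to several outcomes that differ in direction and does not mention recoding.

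The collection of treatment costs and the reference to savings suggest that the hoped-for result is fewer adverse events together with lower spending. In that region the ratio is least informative. At stake is the economic part of the stated hypothesis: a reader given only the ratio could not tell a dominant programme from a dominated one, and could misread the sign when moving from one outcome to the next.

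**Working it through.** **Inputs.** The formula is from Economic analysis. The outcome directions are from Hypotheses, Primary outcomes and Secondary outcomes. The document gives no costs, expected economic effect, threshold or expected ratio, so there is no figure of the plan's own to reproduce. The magnitudes below are assumptions: cost difference 1000 in either direction, effect difference 0.05 in either direction. The trial's listed outcomes are taken as the candidates for the key outcomes.

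**Step 1: the ratio in all four cases.** Write dC for the cost difference and dE for the effect difference on the raw scale. Ratio = dC/dE.

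| Case | dC | Higher is better (e.g. quality of life) | Lower is better (e.g. falls) |
|---|---|---|---|
| Saves money, works | -1000 | -1000/0.05 = -20000 | -1000/-0.05 = +20000 |
| Costs more, works | +1000 | 1000/0.05 = +20000 | 1000/-0.05 = -20000 |
| Saves money, does harm | -1000 | -1000/-0.05 = +20000 | -1000/0.05 = -20000 |
| Costs more, does harm | +1000 | 1000/-0.05 = -20000 | 1000/0.05 = +20000 |

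**Step 2: sign across outcomes (read along the rows).** Each case changes sign between the two columns. The value -20000 means a trade-off on falls, but on quality of life it means that one arm dominates. This holds even if dC contains only programme cost and is always positive.

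**Step 3: value within one outcome (read down a column).** The first and last rows agree in each column: -20000 and -20000, then +20000 and +20000. The two middle rows also agree. This is algebra, since (-c)/e = c/(-e) and (-c)/(-e) = c/e for any c and e. A numerical check over cost differences of 500, 1000 and 5000 and effect differences of 0.01, 0.05 and 0.10 gave equality in all nine combinations. Recoding falls as falls avoided turns the right column into the left one. That cures step 2 but not step 3.

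**Step 4: when step 3 applies.** A negative dC is needed. Programme cost alone is positive, since "The Clinical Mentors and Site Champions will be given paid time of eight hours per week". The first and third rows can therefore arise only if the medical costs listed in Economic evaluation are included. The section's mention of savings suggests that they are. Economic analysis speaks of intervention cost and does not settle it.

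**Step 5: does an alternative separate the cases?** Net benefit = L x (benefit gained) - dC, where L is the willingness to pay per unit of benefit. With an assumed L of 30000, L x 0.05 = 1500, and:
- saves money, works: 1500 + 1000 = +2500
- costs more, works: 1500 - 1000 = +500
- saves money, does harm: -1500 + 1000 = -500
- costs more, does harm: -1500 - 1000 = -2500

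All four cases are distinct and correctly ordered at this L. The documents give no L, so these values only show that the measure separates the cases.

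**The case against.** The formula is the standard incremental cost-effectiveness ratio, and every such ratio has this property. The analyst must compute both differences to form it and will know which case applies. In such a ratio, effect ordinarily means benefit gained. Thresholds, interval methods and dominance rules are commonly left by an article to the full protocol or analysis plan. Cost-effectiveness is also not among the eight numbered hypotheses or the listed primary and secondary outcomes.

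Much of this stands. The absence of a threshold or an uncertainty method is not itself the finding. Reporting the numerator and denominator would resolve the ambiguity, but the section does not commit to it. The point concerns a stated formula applied to outcomes of mixed direction without saying how they are coded.

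The documents do not support four stronger readings that a reader might infer:
- That this ratio is the only economic measure. Economic evaluation names two others, and outcomes per unit of intervention cost has a positive denominator. For one named outcome it separates success from failure (0.05/1500 = +0.0000333 against -0.0000333 at an assumed cost of 1500). Its sign still reverses between outcomes coded in opposite directions.
- That mixed directions cause the shared value. Step 3 holds for any single outcome, so these are two problems, not one.
- That the ratio cannot answer the hypothesis at all. It cannot do so by itself.
- That a frequency of misleading ratios can be given. The documents give no resident numbers, resident-level correlation or costs. If the cost difference is assumed symmetric about zero and independent of effect, that frequency is only the chance that the effect estimate points the wrong way, which would trouble any economic method.

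**Conclusion.** The point holds in a limited form. The sign problem across outcomes holds whichever costs are counted, as long as effects are not recoded as benefit. The shared value for a cost-saving success and a costly failure is exact, but it arises only if resident medical costs enter the numerator. The text suggests this without stating it. Under that reading the ratio by itself cannot support a cost-effective conclusion where the programme both saves money and works.

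The size is qualitative: opposite conclusions share one value. The figure of 20000 follows from assumed inputs and is not an estimate for this trial. The change is worth making because it is cheap and bears on a stated hypothesis. It does not threaten the trial's clinical or staff outcomes.

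**What to change.** In Economic analysis:
- State that the numerator is net cost, meaning the cost of the intervention plus the medical costs listed in Economic evaluation, and bring the two sections into line.
- Name the key outcomes and code each effect as benefit: events or admissions avoided, points gained.
- Report incremental cost and incremental effect separately, each with a 95% confidence interval that allows for clustering by home.
- Base the conclusion on incremental net benefit over a stated range of willingness-to-pay values.
- Give the ratio only where the model is dearer and more effective, or cheaper and less effective, and say which. Otherwise state that it dominates or is dominated.

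This costs a change of wording and a little more analysis of data already planned, with no additional homes, staff or data collection. The one loss is a single headline ratio, replaced by two differences and a net-benefit curve.
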